### Secondary outcomes

#### Qualitative

(i)Norms and cultural factors that influence breastfeeding and other maternal, infant and young child feeding practices. Data will be collected through qualitative interviews with mothers, fathers, community leaders, TBAs, CHWs, other community members, and health care providers(ii)Enabling factors and barriers. Data will be collected through qualitative interviews with mothers, fathers, community leaders, TBAs, CHWs, other community members, and health care providers to identify key players and structures in the community that would facilitate implementation of BFCI; factors that influence uptake of interventions in the community; and any potential hindrances to the success of the intervention (for example, myths, beliefs)

#### Quantitative

(iii)MIYCN knowledge, attitudes and practices according to WHO recommendations on breastfeeding [9]. Data will be collected through self-reports by mothers using an interviewer-administered questionnaire at recruitment and every 2 months during the follow-up period to determine change in knowledge, attitudes and practices with the intervention(iv) Timing of initiation of breastfeeding. Data will be collected through self-reports by mothers using an interviewer-administered questionnaire within the first month of birth(v)Interventions aimed at optimal infant breastfeeding practices have been found to reduce malnutrition among infants and young children. [26]. It is, therefore, expected that the proposed intervention will have an effect on the levels of stunting, underweight and wasting. Anthropometric measurements: weight, length and mid-upper arm circumference (MUAC) will be collected on the child every 2 months during the follow-up period (months 2, 4 and 6). All anthropometric measurements will be carried out by the study staff according to standard procedures [27]. For determination of underweight, stunting, and wasting, weight-for-age *z*-scores (WAZ), length-for-age *z*-scores (LAZ) and weight-for-length *z*-scores (WLZ), respectively, will be generated using the WHO 2006 growth standards [28]. Stunting will be determined as LAZ < −2, underweight as WAZ < −2 and wasting as WLZ < −2 [29](vi)Evidence indicates that breastfeeding is preventive against infections such as rotaviral diarrhea [30]. It is, therefore, expected that promotion of exclusive breastfeeding would impact on the rate of diarrhea morbidity. Data on the presence of diarrhea morbidity in the last 2 weeks for the child will be collected longitudinally through an interviewer- administered questionnaire to the mother every 2 months during the follow-up period (months 2, 4 and 6)(vii) Satisfaction with the intervention, facilitating and limiting factors. Data will be collected through self-administered questionnaire to the mother. Additionally, qualitative interviews will be conducted with the mothers and community members including CHWs on experiences with the intervention

### Data collection and analysis

The study will include both qualitative and quantitative standard data collection procedures. Table 4.

**Table 4 Tab4:** Data collection outline

Formative study		
Study objective	Data/variables	Method
1. To establish local contexts and norms, which influence Maternal, Infant and Young Child Nutrition (MIYCN) practices in order to tailor the intervention package to the local communities	Attitudes and practices regarding breastfeeding and other MIYCN practices; cultural and social factors and norms that influence MIYCN	Focus group discussions (FGDs) with community members (women and men and community health workers); key informant interviews (KIIs) with key informants including community administrators and other leaders (e.g. religious group leaders), traditional birth attendants (TBAs); KIIs with facility health workers, CHWs and Sub-County Health Management (ScHMT) team
2. To identify enabling factors and barriers that may influence the implementation of BFCI and potential ways of addressing them	Key players and structures in the community that would facilitate implementation of BFCI (key influential people in the community, community resource persons that would be involved in the implementation of the project, other useful community resources); factors (e.g. socioeconomic, maternal age, social/family support) that influence uptake of interventions in the community; any potential hindrances to the success of the intervention (e.g. myths, beliefs)	Key informant interviews (KIIs) with key informants including community administrators and other leaders (e.g. religious group leaders), traditional birth attendants (TBAs); KIIs with facility health workers, CHWs and (ScHMT) team, FGDs with mothers and fathers
Cluster randomized trial		
Study objective	Variable/Data	Methods
Primary objective		
1. To determine the effectiveness of the BFCI on the rates of exclusive breastfeeding for the first 6 months	Duration of exclusive breastfeeding as a *derived variable*: age of child, current status of breastfeeding (exclusive, mixed feeding, not breastfeeding) with probes on the age at introduction of other foods or liquids (if appropriate), and a 24-hour recall feeding question	Quantitative: questionnaires to mothers and 24-hour recall at 2, 4 and 6 months;
Secondary objectives		
2. To determine the effectiveness of the BFCI on breastfeeding and other MIYCN knowledge, attitudes and practices	Breastfeeding and other MIYCN knowledge, attitudes and practices including breast positioning attachment, and frequency of feeding	Quantitative: questionnaires to mothers (at baseline and end-line)
3. To determine the effectiveness of the BFCI on rate of initiation of breastfeeding within the first hour of birth	Timing of initiation of breastfeeding with specific prompts on whether infant was put to breast immediately, within 1 hour or later, reasons for the delay in initiation of breastfeeding	Quantitative data gathered from interviews with mothers within 2 months of the birth of the child
4. To determine the effectiveness of the BFCI on nutritional and health status of children aged 6 months and below.	Anthropometric measurements including MUAC, weight and length morbidity from diarrhea using 14- day recall	Quantitative: using questionnaires, MUAC tapes, electronic weighing scale and measuring board at 2, 4 and 6 months
5. To determine satisfaction with the intervention, and the enabling factors/barriers associated with the implementation of the BCFI	Facilitating factors and barriers associated with intervention; Client satisfaction, experiences with intervention and with the processes of delivering it	Quantitative data: Likert scale (satisfaction) at end-line Qualitative: interviews with mothers, community opinion leaders, HWs and CHWs (experiences, facilitating factors and barriers) at midline and end-line

*BFCI* Baby Friendly Community Initiative, *CHWs* community health workers, *HWs* health workers, *MUAC* mid-upper arm circumference

### Qualitative data collection before, during and after the intervention

The qualitative study will involve focus group discussions (FGDs), key informant interviews (KIIs) and in-depth interviews (IDIs) before the intervention, during the intervention and at the end of the intervention. During the formative qualitative study, IDIs (*n* = ~10), FGDs (*n* = ~10) and KIIs (*n* =~20) will be conducted before the beginning of the intervention to: (i) establish knowledge, attitudes and practices regarding maternal nutrition, breastfeeding and complementary feeding; (ii) establish contextual and cultural factors, which contribute towards MIYCN practices; and (iii) inform customization of BCFI including the role of key persons involved in reproductive health such as TBAs.

Focus group discussions will be conducted with women of reproductive age (15–49 years) who are either pregnant, breastfeeding or have ever breastfed and with CHWs and village elders. Key informant interviews will be conducted among health care professionals, sub-County Health Management Team members, TBAs and other community leaders including the chief, village elders and religious leaders. This information will inform the customization of the intervention and the finalization of the quantitative tools for assessing the study outcomes. Key informants will be selected based on their social standing and knowledge of the community in terms of culture and other practices. To identify such individuals, we will talk to the administrative leaders including the chief and the village elders, who will also be considered key informants. These individuals will be included in the formative study since they are in a position to provide useful insight in the structure and ways of the community.

Qualitative data will also be collected during the intervention and at the end of intervention to document experiences and satisfaction with the intervention, challenges and enabling factors, and recommendations for change or future practice. This will be collected through IDIs and FGDs with mothers; and FGDs with CHWs and village elders; and KIIs with other community leaders including religious leaders, health care professionals, TBAs and the Sub-County Health Management Team members.

The qualitative interviews will be tape-recorded after obtaining consent from the participants. Digital recorders will be used for data collection together with notes that will be taken during the interviews. The recorded data will be transcribed verbatim to enhance accuracy.

### Qualitative data analysis

Qualitative data will be transcribed verbatim and coded in NVIVO (QSR International Pty Ltd., Burlington, MA, USA), to identify primary and meta codes and major themes. Themes: for example, regarding breastfeeding and infant feeding beliefs and norms will be identified, with attention to contradiction and diversity of experiences and attitudes. Analysis across all transcripts will be done thematically [31].

### Quantitative data collection

Quantitative data for effectiveness evaluation will be collected at baseline and every 2 months during the follow-up from all mother-child pairs in both intervention and control arms. The target population will be pregnant women and their respective children aged less than 6 months. Baseline data will be collected at recruitment, then follow-up data will be collected every 2 months as appropriate until the respective child is 6 months.

As stated earlier, data collection will involve self-reports by the mother using an interviewer-administered questionnaire, and objective measures through anthropometry (weight, length, MUAC).

Other than the data for the outcomes outlined above, contextual data including household food security, water, sanitation and personal hygiene, antenatal care, delivery characteristics, vaccination, maternal socio-demographic characteristics and socio-economic status (SES) will also be collected using an interviewer-administered questionnaire, administered by a carefully trained research assistant.

Details of quantitative data collection are outlined in Table 4.

### Statistical analysis

Analyses will involve comparison of outcomes between the intervention group and the control group using multilevel linear logistic regression and multinomial logistic models that account for clustering.

Determination of differences between the 2 trial arms in the primary outcome (exclusive breastfeeding) will be done at month 2, month 4 and at month 6. Comparison for other outcomes such as morbidity from diarrhea and malnutrition will also be done at months 2, 4 and 6. Analyses will involve a comparison of differences in the intervention and control groups with regard to the primary outcome (exclusive breastfeeding) and secondary outcomes (other infant feeding practices, diarrhea morbidity and nutritional outcomes), controlling for baseline measures (for example, previous breastfeeding practices) and prognostic factors (for example, SES and household food security) if randomization of the clusters does not control for differences in these factors at baseline, through analysis of covariance (ANCOVA). Statistical methods to determine change will include multilevel linear regression for continuous variables (for example, z-scores, multinomial logistic regression analysis for categorical variables: for example, whether exclusively breastfed at 6 months, 4 months or 2 months [32]. Intention-to-treat analysis [33] will be applied as appropriate. Statistical analysis will mostly be done using Stata (StataCorp, College Station, TX, USA). (See Table 5 for detailed outline of data analysis plan).

**Table 5 Tab5:** Data analysis outline

Formative study				
Study objective	Primary outcome variables	Independent variable	Control variables	Type of analysis
1. To establish local contexts and norms, which contribute to maternal infant and young child nutrition (MIYCN) practices so as to customize the intervention package	Factors that influence breastfeeding and other MIYCN practices	Not applicable	Not applicable	Thematic
2. To identify facilitating factors and barriers that may influence the implementation of BFCI	Facilitating factors and barriers to the implementation of BFCI	Not applicable	Not applicable	Thematic
Cluster randomized trial				
Study objective	Outcome variables	Independent variable	Control variables	Type of analysis
1. To determine the effectiveness of the BFCI on the rates of exclusive breastfeeding for the first 6 months	Exclusive breastfeeding (EBF) at 6 months, 4 months and 2 months	Intervention status	SES, food security, water and sanitation, maternal characteristics, antenatal care	Multinomial logistic regression
2. To determine the effectiveness of BFCI strategy on MIYCN knowledge and attitudes	a. Knowledge levels on MIYCN	Intervention status	SES, food security, water and sanitation, maternal characteristics, antenatal care	Logistic regression
	b. Attitudes on MIYCN			
3. To determine the effectiveness of the BFCI on rate of initiation of breastfeeding within the first hour of birth and its implications on successful EBF for the first 6 months	Initiation of breastfeeding within 1 hour	Intervention status	SES, food security, water and sanitation, maternal characteristics, antenatal care	Logistic regression
4. To assess the change in nutritional and health status among infants and young children from the implementation of BFCI	a. Stunting	Intervention status	SES, food security, water and sanitation maternal characteristics, antenatal care, vaccination status	Logistic regression for stunting, underweight and wasting
	b. Underweight			ANCOVA for *z*-scores and multilevel modeling for diarrhea morbidity
	c. Wasting			
	d. *z*-scores			
	e. Diarrheal and other morbidity			
5. To determine the factors and barriers associated with the implementation of BCFI and how to address them	a. Satisfaction with intervention	Not applicable	Not applicable	Descriptive (Outcome 1)
	b. Experiences with intervention			Qualitative: Thematic analysis (Outcomes 2 and 3)
	c. Limiting and enabling factors			

*ANCOVA* analysis of covariance, *BFCI* Baby Friendly Community Initiative, *SES* socio-economic status

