### Sample size considerations

The sample size determination was undertaken considering the cluster randomized study design [21]. An estimated sample size of 738 mother-child pairs will be required for both intervention and control arms so as to have adequate power to detect an increase in exclusive breastfeeding for 6 months from 32 % (the baseline rate of exclusive breastfeeding in the study setting) [17] to 50 %; an approximately 18-percentage point increase, although higher increases have been documented in similar interventions elsewhere in the developing world [22]. We used a level of precision of 5 % (for a 2-sided *t* test) and power of 80 %. We then adjusted for expected design effect using a design effect of 3.15 calculated based on intracluster correlation coefficient of 0.035 from another study in Kenya (unpublished) and an average cluster size of 62.5. We allowed for 10 % potential loss to follow-up. The estimated sample size is 812. We therefore expect to recruit 406 women in each study arm. Twelve CUs will be required for the estimated sample size.

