The timing of the counseling/support has been found to be important. Prenatal and postnatal breastfeeding counseling interventions, whether alone or in combination have been found effective in improving breastfeeding practices including duration of exclusive breastfeeding and any breastfeeding [36, 37]. In a systematic review of effectiveness of breastfeeding interventions that involved 38 trials [36], prenatal breastfeeding interventions significantly increased the rate of any short-term breastfeeding (1–3 months) rate by 39 % compared to the usual care while combined prenatal and postnatal interventions significantly increased both the rates of intermediate (4–5 months) and long-term (6–8 months) any breastfeeding compared to usual care by 15 % and 33 % respectively. Postnatal interventions significantly increased the rates of short-term exclusive breastfeeding (1–3 months) by 21 %. In another systematic review that involved 20 trials, only interventions with a post-natal component were found to be effective in improving breastfeeding practices while there was no evidence to suggest effectiveness of antenatal counseling/support [37]. This study, which involves home-based and facility-based counseling/support during pregnancy and 6 months following delivery, will provide further evidence on the effectiveness of combined antenatal and postnatal counseling/support on breastfeeding and other infant feeding practices.

Some limitations to this study may include bias in reporting (mothers’ self-report) of the primary outcome (exclusive breastfeeding). To counter this, data will be collected longitudinally at various time points, and a thorough questioning using 24-hour recall on what the baby was fed on will be done to ensure that as true as possible a record of infant feeding practices is obtained. It is possible that even with randomization of clusters; there will be differences in the baseline measures in the intervention and control groups by chance. Analysis methods to be adopted will control for baseline differences, if such differences are identified, but this will reduce the statistical power. Though we do not expect much loss to follow-up as we will work with a stable rural agrarian community, we plan to adopt intention-to-treat analysis to deal with potential loss to follow-up. Additionally, we have included an allowance for loss to follow-up in the sample size determination.

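### Adjustment for covariates depends on observed baseline imbalance in the text but is unconditional in Table 5; the conditional rule picks the primary model after data are seen and gives up power

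*Protocol article*

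**What the plan says.** **Protocol article, Statistical analysis (text).** Outcomes are compared "controlling for baseline measures (for example, previous breastfeeding practices"), and for prognostic factors such as socio-economic status and food security, "if randomization of the clusters does not control for differences in these factors at baseline". No test, threshold or level (mother or cluster) defines such a difference.

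**Discussion, limitations paragraph.** The condition is repeated with a remark on power: "Analysis methods to be adopted will control for baseline differences, if such differences are identified, but this will reduce the statistical power".

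**Table 5.** The text points to this table for the detailed analysis outline. For objective 1, the primary outcome, the control variables are "SES, food security, water and sanitation, maternal characteristics, antenatal care", with no condition attached. Objective 2, "To determine the effectiveness of BFCI strategy on MIYCN knowledge and attitudes", has the same list and logistic regression. The recruitment knowledge and attitude scores are not in it.

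**Secondary outcomes, Quantitative.** Knowledge and attitudes are collected by "interviewer-administered questionnaire at recruitment and every 2 months during the follow-up period to determine change in knowledge, attitudes and practices". Table 4 differs on follow-up timing, "questionnaires to mothers (at baseline and end-line"), but also has a baseline measurement.

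**The concern.** The two rules can give different primary results. Under the text, the model is unadjusted unless an imbalance is found. Under Table 5, it is always adjusted. In a logistic model the adjusted and unadjusted odds ratios generally differ even with perfect balance, so the choice also determines which effect is estimated.

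Choosing covariates by observed imbalance is a poor rule in itself. It ignores how strongly a variable predicts the outcome, and with no criterion it leaves the primary model open until the baseline tables have been read. The power remark makes adjustment look like a cost to be avoided, although for a good individual-level predictor it is a benefit. The same condition governs the recruitment knowledge and attitude scores. These are natural covariates for their own follow-up values and are collected anyway.

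**Working it through.** **1. The plan's own figure.** Inputs from Sample size considerations: power to "detect an increase in exclusive breastfeeding for 6 months from 32"% to 50%, two-sided 5%, power 80%, intracluster correlation (ICC) 0.035, average cluster size 62.5, 10% loss.
- Two proportions, pooled, no continuity correction: 117 per arm.
- Design effect: 1 + (62.5 − 1) × 0.035 = 3.15.
- 117 × 3.15 = 368.6, so 369 per arm and 738 in all. 738 × 1.10 = 812.

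Both stated totals reproduce.

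**2. Where adjustment does cost power.** With 738/12 = 61.5 per cluster, the design effect is 1 + 60.5 × 0.035 = 3.1175. The standard error of the risk difference is √[(0.32 × 0.68 + 0.50 × 0.50) × 3.1175/369] = 0.0629, so the noncentrality is 0.18/0.0629 = 2.86. Noncentral t power:

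| df | No variance explained | 5% of variance explained |
|---|---|---|
| 10 (no cluster-level covariate) | 0.733 | 0.754 |
| 9 (one) | 0.722 | 0.744 |
| 8 (two) | 0.709 | 0.731 |

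Two useless cluster-level covariates cost about 2.4 points. If they explain about 5% of the variance, the loss is recovered (0.731 against 0.733).

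**3. Individual-level covariates.** The article gives no covariate–outcome association, so a range is assumed: one standardised covariate with log odds ratio 0.3, 0.6 or 1.0 per SD and covariate ICC 0.05 or 0.15. The simulation had 12 clusters of 61, rates of 32% and 50%, a cluster-level t test on 10 df, and 10,000 runs per cell. The conditional rule adjusts only if a cluster-level 5% test of the covariate is significant.

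| Covariate ICC | Log OR per SD | Never adjust | Adjust only if imbalanced | Always adjust |
|---|---|---|---|---|
| 0.05 | 0.3 | 0.799 | 0.799 | 0.807 |
| 0.05 | 0.6 | 0.798 | 0.803 | 0.842 |
| 0.05 | 1.0 | 0.797 | 0.807 | 0.896 |
| 0.15 | 0.3 | 0.780 | 0.782 | 0.807 |
| 0.15 | 0.6 | 0.738 | 0.744 | 0.838 |
| 0.15 | 1.0 | 0.669 | 0.683 | 0.889 |

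- Always against never: from 0.807 − 0.799 = 0.8 points to 0.889 − 0.669 = 22 points.
- Conditional against never: from 0 to 0.683 − 0.669 = 1.4 points. The condition was met in only about 5% of trials.
- Type I error under the conditional rule: 0.040 to 0.053.

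The ICC of 0.035 was set on the logit scale here, so some unadjusted values lie above the 0.733 of step 2. Compare within rows.

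**4. How the gain arises in a logistic model.** In an individual-level simulation (n = 738, no clustering, log odds ratio 0.6 per SD), the standard error of the log odds ratio went from 0.152 unadjusted to 0.159 adjusted, while the mean z rose from 4.56 to 4.73. Power rises because the conditional effect is larger, not because the standard error is smaller.

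**5. Knowledge and attitudes.** The scores are taken at recruitment in order to determine change. The objective 2 model in Table 5 has no recruitment score. The text's baseline measures could cover it, but at most under the imbalance condition.

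**The case against.** The best defence is that Table 5 is the detailed plan. If it governs, there is no imbalance test for the primary outcome and no power is given up. If it is only a list of candidates under the text's condition, there is one rule and not two. Either reading is possible, but the article does not say which applies, and the Discussion restates the condition. So the need to reconcile them stands, and it would be wrong to say flatly that covariates enter only on imbalance.

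A second defence is that the exact covariates and the imbalance criterion are normal analysis-plan content, and that the baseline measures are given only by example and could include knowledge scores. That is fair for missing detail. It does not cover a conditional rule that the article states twice.

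Several stronger readings are tempting but unsupported:
- *That power loss is the protocol's reason for the condition.* The Discussion names it as a drawback of adjusting. The Statistical analysis section gives no such reason.
- *That adjustment never costs power.* Step 2 shows that it can with 12 clusters.
- *That some imbalance is bound to trigger adjustment.* Five independent 5% tests that respect clustering give 1 − 0.95⁵ = 23%, and fewer if the covariates are correlated. A much higher rate needs tests that ignore clustering, which the article does not propose.
- *That type I error is inflated.* The simulation, with one covariate, did not show it.
- *That adjusting for the recruitment score saves a calculable share of residual variance.* That formula is for a linear model. Table 5 lists logistic regression, and no correlation is given.

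**Conclusion.** The point holds in this form. The text and Table 5 give different rules for the primary exclusive breastfeeding analysis. The conditional rule has no criterion, fixes the model after data are seen and forgoes nearly all the power that adjustment can offer: gains of at most about 1.4 points, against 0.8 to 22 points for always adjusting. Those sizes rest on assumed covariate strengths and ICCs and on one covariate in a cluster-level analysis; the direction was the same in all six scenarios. The power sentence in the Discussion is too general rather than wrong in every case: the loss applies mainly to cluster-level or weakly prognostic covariates and is about 2.4 points for two cluster-level ones. The omission of the recruitment score from the knowledge and attitude models is a mismatch with the stated aim of determining change; its size cannot be given from the article. The harm is an open primary model and lost power, not a demonstrated false-positive problem. This should be corrected.

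**What to change.** - Remove the imbalance condition from the Statistical analysis section and the Discussion.
- State that the primary model always adjusts for a short, named set measured at recruitment and drawn from variables the article already lists, whatever the observed balance. An example is socio-economic status, food security, named maternal characteristics, and previous breastfeeding practice with a separate category for first births. Report the unadjusted result beside it.
- For knowledge and attitudes, always include the recruitment score as a covariate.
- Rewrite the control-variable column of Table 5 to match.
- Delete the power sentence, or limit it to cluster-level covariates.

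The cost is wording only: no new data and no change in sample size. The downside is small. The set must be named before data are seen, and a covariate that turns out weak adds little.

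### Table 5 omits the clustering that the text promises and gives the yes/no primary endpoint a multinomial model; followed literally, its primary test would have a type I error of about 27%

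*Protocol article*

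**What the plan says.** Under Primary outcome, the protocol article defines the endpoint as the proportion of children exclusively breastfed for the first 6 months, to be compared between arms. Sample size considerations treats it as binary: the trial is sized to "detect an increase in exclusive breastfeeding for 6 months from 32" % to 50 %. Twelve community units (CUs) are randomised, six per arm.

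The Statistical analysis section first commits to "multilevel linear logistic regression and multinomial logistic models that account for clustering". Later in the same section it assigns "multinomial logistic regression analysis for categorical variables: for example, whether exclusively breastfed at 6 months, 4 months or 2 months", and multilevel linear regression to continuous variables such as z-scores. It then sends the reader to Table 5 for the detailed plan.

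Table 5 lists:
- exclusive breastfeeding at 6, 4 and 2 months: multinomial logistic regression;
- knowledge and attitudes, and initiation within 1 hour: logistic regression;
- nutritional status: "Logistic regression for stunting, underweight and wasting";
- z-scores and diarrhoea: "ANCOVA for *z*-scores and multilevel modeling for diarrhea morbidity".

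The word multilevel appears in Table 5 for diarrhoea only. The abstract also lists ANCOVA, multinomial logistic regression and multilevel modelling, without saying which applies to which outcome.

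**The concern.** There are two problems, and both can be seen in the article itself.

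First, text and table disagree on clustering. The table uses the word multilevel for one outcome, so its absence from the others can fairly be read as deliberate. An analyst who programmes from the table would treat children in the same CU as independent. The plan's own design effect implies that standard errors would then be too small by a factor of √3.15 = 1.77. The trial is meant to inform the roll-out of the programme in Kenya, so a false claim of effectiveness would matter.

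Second, the model named for the primary endpoint does not fit it. With two levels, a multinomial model is ordinary logistic regression. With more levels, for example the three feeding states in Table 4 (exclusive, mixed, not breastfeeding), it produces several contrasts, and the article does not say which one is primary. No outcome categories are defined for the model.

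**Working it through.** **Inputs, from Sample size considerations and Study design and randomization.** Two-sided 5% level, 80% power, 32% v 50%, ICC 0.035, average cluster size 62.5, design effect 3.15, 10% loss to follow-up, 12 clusters.

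**Step 1: reproduce the plan's own figures.**
- Design effect: 1 + (62.5 − 1) × 0.035 = 3.1525, stated as 3.15.
- Per arm without clustering: [1.96 × √(2 × 0.41 × 0.59) + 0.8416 × √(0.32 × 0.68 + 0.50 × 0.50)]² / 0.18² = 116.02, rounded up to 117; 234 in total.
- With clustering: 234 × 3.15 = 737.1, so 738 as stated. Then 738 × 1.10 = 811.8, so 812 as stated.

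The plan's sample size therefore rests on a binary endpoint and a clustered design.

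**Step 2: set text against table.**

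| Outcome | Text | Table 5 |
|---|---|---|
| Exclusive breastfeeding (primary) | multinomial, accounting for clustering | multinomial, no cluster term |
| Knowledge/attitudes, early initiation | models accounting for clustering | logistic |
| Stunting, underweight, wasting | models accounting for clustering | logistic |
| z-scores | multilevel linear | ANCOVA |
| Diarrhoea | models accounting for clustering | multilevel |

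Only the diarrhoea row agrees on clustering.

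**Step 3: type I error if the table is followed literally.** A test that ignores clustering has a true standard error √DE times the one it uses, so its error rate is 2[1 − Φ(1.96/√DE)].
- ICC 0.035, DE 3.15: 1.96/1.775 = 1.104, giving 26.9%.
- ICC 0.02 (assumed), DE = 1 + 61.5 × 0.02 = 2.23: 18.9%.
- ICC 0.01 (assumed), DE = 1 + 61.5 × 0.01 = 1.615: 12.3%.

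Simulations under no effect (12 clusters of about 62, 32% in both arms, ICC 0.035) gave 25.6% to 27.0%.

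**Step 4: type I error if the text is followed, with large-sample inference.** The reference distribution is an assumption here, because the article states none.
- Random-intercept logistic model, Wald z: 8.2% in a run of 1,500 (Monte Carlo standard error √(0.082 × 0.918/1,500) = 0.7 points), and 9.2% to 10.5% in the other runs, the largest being 8,000.
- Same model, likelihood-ratio test: 6.5% to about 8%.
- Uncorrected cluster-robust variance with z, one way to let a multinomial model account for clustering: P(|t₁₀| > 1.96 × √(5/6)) = 10.4%; with the usual 12/11 factor, 9.1%.

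Rounded, this is about 7% to 10%.

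**Step 5: methods suited to 12 clusters, same setting.**
- t-test on the 12 cluster proportions, 10 df: 5.0% to 5.2%.
- Random-intercept logistic model referred to t on 10 df: 5.3% to 6.9%.

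**The case against.** The strongest reply is that the text already settles the matter. Its opening sentence covers the multinomial models as well as the logistic ones, the sample size carries a design effect, and the last column of Table 5 can be read as shorthand for model families beneath that general statement. Nowhere does the article say that clustering will be ignored. This stands. A reader might infer that the plan's type I error is 10% to 27%, and the article does not support that. The 27% needs the table to override the text. It also needs the ICC to be right, and that is an "intracluster correlation coefficient of 0.035 from another study in Kenya (unpublished") figure.

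A reader might also fault the plan for having no small-sample correction. The article names no reference distribution or degrees of freedom, but a condensed protocol article commonly leaves these to the analysis plan, so their absence is not a finding. The 7% to 10% shows only why the reconciled wording should name a suitable method.

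Nor does the multinomial label inflate type I error by itself. With two levels it is logistic regression. With three, the difference in exclusive breastfeeding can still be obtained from fitted probabilities, and Table 4's three-level feeding status is a plausible origin of the label, though the article does not say so. What remains is that the categories and the primary contrast are undefined.

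Finally, one might call ANCOVA invalid because no z-score precedes month 2. The text uses ANCOVA to adjust for covariates in general, such as earlier breastfeeding practices, socio-economic status and food security, so it needs no baseline z-score. The conflict with multilevel linear regression remains.

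**Conclusion.** The point holds as an internal contradiction about the primary analysis, together with a model that does not fit the endpoint. The text promises models that account for clustering; the table it calls the detailed outline shows that for diarrhoea alone. The yes/no primary endpoint gets a multinomial model with undefined categories.

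The size is conditional. Table 5 taken literally gives about 27% type I error at ICC 0.035, and 12% to 19% at assumed ICCs of 0.01 to 0.02. The text's approach gives about 7% to 10%, assuming large-sample inference. Both sets of figures assume 12 clusters of about 62 children and, in the simulations, a true rate of 32% in both arms. The two readings differ enough that the contradiction should be resolved before any analysis by arm.

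**What to change.** 1. Make Table 5 match the text: every outcome analysed with a method that accounts for CU. This covers exclusive breastfeeding, knowledge and attitudes, initiation, stunting, underweight, wasting and z-scores as well as diarrhoea.
2. In the abstract, the Statistical analysis text and Table 5, replace the multinomial model for the primary endpoint with one binary analysis suited to 12 clusters, and report the difference in proportions with its confidence interval. A t-test on cluster proportions with 10 df is one valid choice. A mixed logistic model with a small-sample degrees-of-freedom correction is another, though referring the Wald statistic to t on 10 df gave 5.3% to 6.9% above, so the exact correction should be named.
3. For z-scores, choose one model in place of the two now named, with covariates listed if adjusted. Child anthropometry starts at month 2, so describe the results as differences between arms at months 2, 4 and 6, not as change.

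The cost is wording and a little programming. Confidence intervals will be wider than those of an analysis that ignores clustering.
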